**Produced by Gulou Hospital of Nanjing University School of Medicine**

**Programs Programs Abstract Summary**

| Project name | Accuracy study of trans-thoracic wall cardiac ultrasound (TTE) guided real-time localization of central venous catheter tip |
| --- | --- |
| Purpose of the study | a. To establish the technique of real-time positioning of catheter tip by cardiac ultrasound and optimize the operation procedure;  b. Conduct clinical studies to further investigate the consistency of trans-thoracic wall cardiac ultrasound localization of central venous catheter tip position and postoperative CT. |
| Study design | Diagnostic study |
| Total number of cases | 30 cases |
| Case selection | *Inclusion Criteria*  *Malignant tumors proposed for cyclic infusion of chemotherapeutic agents requiring placement of PICC, PORT catheter;*  *Patients aged >18 years old;*  *Agree to participate in this study and sign the informed consent for this study.* |
|  | *Exclusion criteria*  *Patients who cannot tolerate ultrasound monitoring after recent major chest surgery;*  *Patients who cannot tolerate CT examination;*  *Patients with contraindications to central venous catheter placement ;*  *Suffering from thrombophilia;*  *Those with abnormal coagulation function.* |
| Treatment Options | Those who signed the informed consent and met the inclusion and exclusion criteria were enrolled.  Patients requiring central venous catheterization  Undergoing TTE-guided catheterization |
| Evaluation of efficacy | *Indicators of effectiveness evaluation (primary and secondary outcome indicators)*   1. *Primary outcome indicators:*   *Precision of catheter tip localization (accuracy)*   1. *Secondary outcome indicators:*   *Surgical time, economy* |
|  | *Safety evaluation indicators*  *Incidence of surgical site infection, incidence of intraoperative adverse events, catheter ectasia* |
| Statistical methods | SPSS 20.0 statistical software was used to perform t-test, xo2 test and Fisher's exact test to analyze the safety, efficacy and economy. |
| Study period | 2023.04 to 2024.12 |

Table of Contents

[I. Background of the study 5](#_Toc110801521)

[Purpose of the Study 7](#_Toc110801522)

[III. Types of Study Design, Principles and Experimental Steps 7](#_Toc110801523)

[Case selection 9](#_Toc110801524)

[V. Research Methods and Technical Route 9](#_Toc110801525)

[Observation items and testing time point 12](#_Toc110801526)

# Background

The central venous catheter is the first line catheter for chemotherapy administration and parenteral nutrition ^([) (1) (~2) (])^; the tip position of the central venous catheter is very important, and the diagnosis of catheter tip ectasia after the placement of the catheter implies the need for tip repositioning, which will increase the risk of infections, radiological injuries, and greater healthcare expenditures ^([) (3) (])^. According to the INS infusion guidelines ^([) (4) (])^, the central venous catheter tip should be optimally positioned in the lower 1/3 of the superior vena cava at or near the CAJ, and catheter tip ectasia can result in varying degrees of complications.

With the development of technology, new catheter localization techniques are emerging, and the localization techniques that are widely used in the clinic include in vitro measurement, imaging localization, and intracavitary electrocardiographic localization ^([) (5])^.

In vitro measurement is to measure the length from the pre-positioning site to the third intercostal space, of which the most traditional method is to measure the length from the puncture point to the right sternoclavicular joint, and then the length from the right sternoclavicular joint downward reflexed to the third intercostal space, in the patient's prone position, with the arm positioned at 90° to the body ^([) (6) (])^. Later on, some scholars have continuously improved the extracorporeal measurement method, such as the one-line measurement method, the elbow transverse measurement method, the caliper (formula) measurement method and so on ^([) (7) (])^, but the variability of these measurements is large, which is not enough to guide clinical practice, and some researchers believe that the extracorporeal measurement method is greatly affected by the patient's height, arm length, and the width of the rib cage, and therefore can only be used as a preliminary prediction of the depth of placement of the catheter^([) (8) (]).^ .

Imaging localization methods include pre-catheterization chest radiography and post-catheterization chest radiography. The pre-tube placement method ^([) (9) (])^refers to the preoperative chest X-ray, the distance from the right sternoclavicular joint to the sixth thoracic vertebra is measured on the chest radiograph, and the distance from the puncture point to the right sternoclavicular joint is added to the distance from the puncture point to the right sternoclavicular joint when the patient is in the lying position with the arm at 90° to the body, and the sum of these two distances is the length of the tube placement. Post-catheterization chest radiography is considered the "gold standard" for positioning the tip of the central venous catheter ^([) (5) (])^. X-ray chest radiographs are taken after the completion of catheterization, and professionals determine whether the tip of the catheter is ectopic or not through the chest radiographs, and if it is ectopic, the position of the catheter tip is adjusted according to the ectopic condition and the judgment of professionals.

Intraluminal electrocardiogram localization method is a hot spot of research at home and abroad at present. This method is based on the theory of electrical activity of the heart and relies on the judgment of changes in electrical signals within the lumen to locate the catheter tip in the central vein ^([) (10])^. Studies have shown that the intracavitary ECG-guided catheter tip localization is more precise than in vitro measurements and X-ray localization techniques ^([) (11) (~12) (])^. Moreover, the endocavity ECG method can be operated at the bedside, real-time localization is achieved, there is no radiological injury, and it can be applied to pregnant women, children, and neonates, and it reduces the incidence of related complications^([) (1) (3) (~1) (~1) (4) (])^.

In addition, there are ultrasound localization method, electromagnetic navigation localization technology, central venous pressure localization method. Among them, ultrasound localization method can realize real-time localization at the bedside and is easy to operate, with less damage to patients. According to the research of domestic scholars, the sensitivity of trans-thoracic wall echocardiography (TTE) in catheter tip localization is as high as 98.6% ^([) (1) (5) (])^, but ultrasound interpretation relies on ultrasound-qualified professionals, and the technology lacks the corresponding technical specifications. Electromagnetic navigation localization technique ^([) (1) (6) (~1) (7) (])^ is currently more widely used in foreign countries, This method borrows sensors to sense the magnetic field generated by the guidewire in the catheter, and the operator can observe the position of the guidewire through the monitor, which is also a kind of real-time localization technique, has a high localization accuracy rate^([) (1)(8) (])^, but fewer studies have been carried out in China on the related technology. Central venous pressure localization method ^([) (1) (9) (])^ is to use the principle that the central venous pressure of the superior vena cava vein is 5~12cmH_2_O. After delivering the central venous catheter, connecting the tee tube and measuring the central venous pressure (CVP), if the CVP< is 12cmH_2_O, it proves that the tip of the catheter arrives at the superior vena cava vein.

In clinical practice, our team has found that although there are various techniques for catheter tip positioning, there are still cases of difficult and imprecise positioning. Combined with this, our team has used transthoracic cardiac ultrasound (TTE) to assist catheter tip positioning in the process of catheter placement, which has achieved good results.

TTE can make up for the shortcomings of chest X-ray, which is unable to locate the catheter tip in real time and has radioactive damage. Although chest X-ray has been considered the "gold standard" for central venous catheter tip localization ^([) (20) (])^, it also has certain shortcomings. Firstly, in terms of the accuracy of localization, chest X-ray cannot directly show the exact position of the CAJ, and it is necessary to indirectly determine the position of the tip of the catheter through the anatomical marking of the image, and under the influence of the patient's respiratory movement, the position of the tip of the catheter will move up and down along with respiratory movement, which reduces the accuracy of the localization of the chest X-ray ^([) (4) (])^. Second, chest X-rays have a certain amount of radioactive damage to the body, while TTE does not have such damage. Finally, chest radiographs need to be taken in the imaging department, so it is difficult to quickly transfer the patient to take chest radiographs to explore the catheter position if there is difficulty in placing the catheter during the placement process; in addition, after the end of the placement, if chest radiographs are taken to show that the tip of the catheter is poorly positioned, it is necessary to adjust the position of the catheter tip for a second time, which increases the risk of infection and the cost of treatment.

TTE can be used in patients with unstable waveforms on intraluminal ECG, insignificant P waves or no P waves. Intraluminal ECG positioning techniques are affected by individual differences, and there is no conclusive evidence regarding the relationship between changes in intraluminal ECG P-wave morphology and catheter tip position, and there are difficulties in eliciting characteristic P waves ^([) (21])^. In addition, according to the 2021 edition of the INS Infusion Therapy Guidelines, intracavitary ECG is prohibited for use in patients with no P waves or abnormal cardiac rhythms, whereas TTE compensates for the shortcomings of intracavitary ECG localization at this point.

Based on the previous clinical practice, i.e. TTE was used to investigate the catheter tip position when the catheterization nurse had difficulty in locating the catheter, the research team accumulated the corresponding clinical experience and kept the data for analysis, and the following findings were made: i. TTE locates the catheter tip position visually. ii. Usually, the patient performs cardiac ultrasonography in the left lateral recumbent position. Due to the limitation of the catheterization position, we tried to observe the patient in the lying position from different views (short-axis view of the great arteries, four-chambered cardiac view, and subxiphoid bi-atrial view), and we found that the visibility of the three views was 60%, 80%, and 10%, respectively, and therefore we took the four-chambered cardiac view as the standard view for observation; second, the selection of the time point for observation. We found that when the catheter was determined to be in the right atrium, the position of its tip was changing with the cardiac cycle, and it was necessary to select the time point as a standard. After statistical analysis, we found that the length of the catheter into the right atrium was most accurately estimated based on the distance from the tip of the catheter to the interventricular septum at the end of the atrial systole period, VL2 (see Appendix for study data).

# Purpose of the study

1. primary purpose: to establish real-time cardiac ultrasound localization technique and to establish a standardized operating procedure (SOP) for this technique

2. secondary purpose: to conduct a clinical study to further validate the accuracy of trans-thoracic wall cardiac ultrasound localization of the catheter tip.

# III. Types of study design, principles and experimental steps

1. Study design

1. Type of study design: Diagnostic study
2. Research center: Nanjing Gulou Hospital Jiangbei Branch

2. Indications

Patients with malignant tumors requiring central venous catheterization for cyclic infusion of chemotherapy drugs; patients >18 years old; patients who agree to participate in the study and sign the informed consent form.

3. Endpoints

Patients' post-catheterization CT images.

4. Procedure

Patients sign an informed consent form

Screening

Failure

Withdrawal

Success

TTE is used to localize the catheter tip during catheterization.

Primary efficacy measures

Secondary efficacy measures

Safety evaluation

End of trial

Detection of catheter tip position by CT after catheterization

#

# Case selection

1. Number of cases

It was planned to enroll 30 subjects in our Comprehensive Oncology Center for this study.

1. Inclusion Criteria
2. Those with malignant tumors who are proposed to undergo cyclic infusion of chemotherapeutic agents requiring placement of PICC, PORT catheter;
3. Patients aged >18 years;
4. Agreed to participate in this study and signed the informed consent for this study.
5. Exclusion criteria
6. Patients who cannot tolerate ultrasound monitoring after recent major chest surgery;
7. Patients who cannot tolerate CT examination;
8. Patients with contraindications to central venous catheter placement;
9. Patients with thrombophilia;
10. Those with abnormal coagulation function.
11. Exclusion Criteria

Patients who did not use TTE to locate the catheter tip after enrollment.

1. Criteria for termination of the trial

Patients with intolerance during catheterization were unable to complete the trial.

# V. Research Methods and Technical Route

1. Subject enrollment

Patients were enrolled in the order of catheterization.

1. Intervention/Study drug name and specification

In this study, trans-thoracic wall cardiac ultrasound was used to locate the position of the catheter tip, all intraoperative ultrasound exploration steps were done by one doctor, tube placement steps were done by one nurse, and postoperative CT examination was performed in the imaging department of our hospital.

(1) Instruments

Ultrasonic instrument

(2) Methods

Ultrasound localization catheter tip operation procedure:

a. Patient position preparation: the patient takes a flat lying position, and the catheterization arm is placed at 90° to the torso;

b. Disinfecting and spreading the towel: measure the arm circumference, disinfect the catheter placement site, and spread the towel;

c. Placement of catheter: the catheterization nurse punctures the needle under ultrasound guidance and places the catheter;

d. Cardiac ultrasound-assisted catheter tip localization: ultrasound probe to explore the four-chambered heart section, observe the imaging effect (if the observation effect is not good, observe the short-axis section of the great arteries and subxiphoid section in turn), ultrasound doctor and the placement nurse to cooperate with the placement nurse to send the catheter until the doctor can observe the tip of the catheter under the ultrasound, retain the image to calculate the distance between the tip of the catheter and the septum at the end of cardiac contraction period, L, and the placement nurse to pull out the catheter to the outside. The catheterization nurse pulls the catheter outward for the length of L.

e. Proper fixation of the catheter: The placement nurse continues to complete the subsequent steps to properly fix the catheter.

3. Research intervention program

After patients signed the informed consent form, those who met the inclusion and exclusion criteria were enrolled;

Subjects received TTE-guided catheter placement, and the catheter tip position and procedure time were recorded during placement;

At the end of catheter placement, subjects had CT taken;

The patients were followed up postoperatively for the occurrence of complications (infections);

Analyzing whether there is consistency between TTE-guided catheter tip positioning and CT.

| Personnel Assignment | Assignment |
| --- | --- |
| One physician | Responsible for the ultrasound localization part of the catheter placement process. |
| One catheterization nurse | Responsible for the catheterization process, cooperating with the doctor to complete the tip positioning. |
| One recorder | A recorder is responsible for recording data on site. |

4. Combination of drugs

This study does not involve the combination of drugs.

5. Research Flowchart

| Trial Flow Chart | | | |
| --- | --- | --- | --- |
| Window period  Trial Procedure | Visit 1  Screening period | Visit 2  Trial period | Visit 3  Observation Period |
|  | -1~0 days | 1 day | 2~ 3 days |
| Signed informed consent | × |  |  |
| Demographic information | × |  |  |
| Medical history and treatment history | × |  |  |
| Determination of inclusion/exclusion criteria | × |  |  |
| Randomization | × |  |  |
| Body temperature | × | × | × |
| Catheter placement |  | × |  |
| Observation and documentation of catheter tip position |  | × |  |
| CT examination |  |  | × |
| Complications | × | × | × |
| Adverse events |  | Continuous observation | |
| Surgical time |  | × |  |
| Nurse Confidence Index |  | × |  |
| Study Summary |  | × | |

6. Study-related laboratory tests

Blood tests (RBC/WBC/PLT/HBG) and coagulation tests (PT/APTT/FIB/D-Dimer/INR) will be completed during the screening period. During the trial and observation periods, if patients develop high fever and are reasonably suspected of having catheter-associated infections, blood cultures are required to confirm the diagnosis of catheter-associated infections.

7. Study-related imaging

Postoperative chest CT should be performed to confirm the location of the catheter tip under imaging.

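### The protocol specifies no TTE reading of the final tip position, so the CT-based primary proportion measures success of TTE-guided placement, not agreement between TTE and CT

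*Protocol*

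**What the plan says.** **Order of events (section V, item 2(2)).** In step d the catheter is advanced "until the doctor can observe the tip of the catheter under the ultrasound, retain the image to calculate the distance between the tip of the" (this tip-to-septum distance is called L). Then "The catheterization nurse pulls the catheter outward for the length of L". In step e, "The placement nurse continues to complete the subsequent steps to properly fix the catheter". Neither step describes a TTE image after the withdrawal or after the fixation.

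**Recording.** Item 3 of section V says "the catheter tip position and procedure time were recorded during placement". The flow chart in item 5 has a single row, "Observation and documentation of catheter tip position", marked at Visit 2 with no moment given within the visit.

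**Promised comparison.** Purpose b in the summary is to "further investigate the consistency of trans-thoracic wall cardiac ultrasound localization of central venous catheter tip position and postoperative CT". Item 3 of section V lists "Analyzing whether there is consistency between TTE-guided catheter tip positioning and CT". The study is labelled diagnostic, and its secondary purpose is to validate the accuracy of TTE localization.

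**Primary endpoint (section VII).** A subject counts as accurate if postoperative CT shows the tip at the CAJ or in the lower third of the SVC. The endpoint is the number of such subjects divided by the total sample. No TTE reading enters the formula.

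**Time of CT.** Section VII has CT immediately after the operation, and section VI puts tip precision on the day of surgery. The flow chart puts CT at Visit 3, days 2 to 3.

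**The concern.** A consistency analysis needs two readings of the same thing: where TTE says the tip is and where CT says it is. The only TTE measurement described is taken before the last two catheter movements, while CT shows the result after them. TTE contributes a length, and the final position is that length carried out by hand.

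The conclusion about the technique is at stake. A tip found off target on CT could come from a wrong L, from a pull-back that differed from L, or from movement during fixation. The first is a fault of the TTE measurement and the other two are faults of handling. An SOP, which is the study's primary purpose, would be corrected in different places depending on the cause. If the proportion is reported as TTE-CT consistency, readers will take it as evidence about the ultrasound reading alone.

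**Working it through.** The protocol gives no figure to reproduce here, and 30 is stated without a derivation. The check is on what the planned data can identify.

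**1. What makes up the CT result.** Measure positions in cm beyond the CAJ, positive meaning deeper.
- T = true length of catheter beyond the CAJ when the TTE frame is stored
- L = the TTE estimate (the Background treats the tip-to-septum distance as an estimate of the length inside the right atrium)
- W = length withdrawn in step d
- F = net length withdrawn as read after fixation
- M = movement between fixation and CT, plus CT reading error
- D = tip position on CT

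Then D = T − F + M = (T − L) + (L − W) + (W − F) + M.

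The terms are TTE measurement error, pull-back error, fixation movement and later movement. The primary endpoint uses only whether D falls in the target zone. W and F are not among the observations listed in sections V to VII, so the terms cannot be separated. The terms can also cancel: a pull-back error can offset a wrong L, so no direction of bias follows.

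**2. Could L serve as the TTE result without the withdrawn length?** The TTE-implied final position is L − F. If F is not recorded and is taken to equal L, the implied position is 0, on target, for every subject. The TTE-by-CT table then has one row. With x of 30 on target by CT:
- Observed agreement = x/30, which is the primary proportion itself.
- Chance agreement = 1 × (x/30) + 0 × (1 − x/30) = x/30.
- Kappa = (x/30 − x/30) / (1 − x/30) = 0 for any x below 30, and undefined at x = 30.

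A categorical consistency analysis built this way adds nothing to the primary proportion.

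**3. The proportion does not split into its causes.** As a simple model, let p be the probability that L is right and h an independent probability that handling spoils a right L. The observed proportion is p × (1 − h). Take a hypothetical 27/30 = 90% (exact 95% interval 73.5% to 97.9%):
- p = 100%, h = 10%: 1.00 × 0.90 = 90%.
- p = 90%, h = 0%: 0.90 × 1.00 = 90%.

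The data fit both equally well, and more subjects would narrow the interval without separating them. This shows non-identifiability only. It does not estimate how large handling error is.

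**4. What recording L, W and F would give.** L − W and W − F become known for each subject. The remainder, D − (L − F) = (T − L) + M, is TTE error plus later movement. It approximates TTE error only if M is small, and that depends on whether CT is taken immediately or on days 2 to 3. It also assumes that length moved at the skin equals length moved at the tip.

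**The case against.** **The pull-back is part of the technique.** Withdrawing by L is how TTE brings the tip to target, and CT checks the outcome. This stands in full: as a measure of placement success, the primary proportion properly includes pull-back and fixation. A reader might infer that the endpoint wrongly charges handling error to TTE. Section VII does not support that, because no TTE reading enters its definition. The fault lies in calling the result consistency or accuracy of TTE localization.

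**Silence is not exclusion.** A reader might infer that TTE never sees the final position. The protocol does not say so. Tip position is recorded at some point during placement, the flow-chart row has no moment within Visit 2, and step d is garbled in translation (the pull-back appears twice). What stands is narrower: no such reading is specified. Where an SOP is the main product, an unspecified look cannot be relied on to be made or recorded uniformly.

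**The case form may already hold the lengths.** It is not shown, so this is possible. The protocol's own lists of observations do not name them.

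**A final TTE look may seem the obvious cure.** It would make a poor index test. The views described are for seeing a tip in the right atrium, whereas a correctly withdrawn tip lies at the CAJ or in the SVC. The Background reports visibility of 60%, 80% and 10% for the three views, so a tip may be unseen because it is on target, because it is withdrawn too far, or because the view failed. More probe time also has a cost: pain from probe pressure is the one adverse event the protocol describes, and surgical time, a secondary endpoint, runs until fixation.

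**Conclusion.** The point holds in a limited form. The only TTE measurement described precedes withdrawal and fixation, and no TTE reading of the final position is specified. The promised TTE-CT consistency therefore has no defined TTE side. The primary proportion is a valid measure of TTE-guided placement success but does not show agreement of a TTE reading with CT, and a miss on CT cannot be traced to its cause.

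This applies to all 30 planned subjects. It changes what may be concluded, not whether the proportion can be computed. No numerical bias is claimed, because the protocol gives neither the width of the target zone in cm nor any figure for handling error, and errors may offset. The verdict rests on reading steps d and e as the complete procedure. If the case form already records the lengths or a timed final reading, what remains is to state the pairing and the wording of the claim.

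**What to change.** 1. For every subject record L, the view used, and the catheter's external markings before withdrawal, after withdrawal and after fixation. These give W and F. For PORT catheters, state at which step the last length is read, since the markings may not be readable once the system is implanted.
2. Define the TTE-implied final position from L and the recorded withdrawal, and compare it with CT. This needs a signed distance from the CAJ on CT beside the on-target classification. Report L minus the withdrawn length separately, so that handling error is visible.
3. Describe the primary proportion as success of TTE-guided placement, and reserve the term consistency for the comparison in item 2.
4. Optionally, record a brief look after withdrawal by the same doctor as a descriptive check for a tip still visible in the right atrium. It should not be the index test.
5. Reconcile the CT time between sections VI and VII and the flow chart. Also reconcile the cardiac time point for L, which is the end of atrial systole in the Background and the end of cardiac contraction in step d.

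**Cost.** Items 1 to 3 need a few extra form fields, one more CT measurement and a more modest claim, with no added staff or equipment. Item 4 adds some probe and procedure time.
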